## Abstract

**Introduction:**

Stellate ganglion block has been reported to expand cerebral vessels and alleviate vasospasm after aneurysmal subarachnoid hemorrhage. However, the causal relationship between early stellate ganglion block and cerebral vasospasm prevention has not yet been established. The purpose of this study was to explore the effectiveness and safety of early stellate ganglion block as a preventive treatment for cerebral vasospasm and delayed cerebral ischemia.

**Methods/design:**

This is a single-center, prospective, randomized, controlled, blinded endpoint assessment superiority trial. A total of 228 patients will be randomized within 48 h of aneurysmal subarachnoid hemorrhage onset in a 1:1 ratio into two groups, one group receiving an additional e-SGB and the other group receiving only a camouflaging action before anesthesia induction in the operating room. The primary outcome is the incidence of symptomatic vasospasm within 14 days after aSAH. Further safety and efficacy parameters include the incidence of radiographic vasospasm, new cerebral infarction, postoperative delirium, and complications up to 90 days after surgery; postoperative cerebral hemodynamics; Mini-Mental State Examination score; modified Rankin scale score; and all-cause mortality up to 90 days after surgery.

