### Patient population

#### Inclusion criteria

Patients with aSAH diagnosed by imaging (CTA or DSA) and scheduled for surgical intervention within the expected time period (48 h) will be assessed for recruitment. Those with an onset more than 48 h prior to assessment will not be included because CVS can occur on the third day after onset. The inclusion criteria were as follows: (i) 18 years ≤ age ≤ 65 years, (ii) planned aneurysm clipping, (iii) preoperative Hunt-Hess grade 1–3, and (iv) signed informed consent.

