### Measurements

The endpoint assessors, who are only responsible for postoperative follow-up, will regularly visit all patients at the planned time points (Table 1). The nurse will check the patients every 4 h. At 10:00 AM every day, the attending neurologist and nurse will evaluate whether the patient experienced symptomatic vasospasm in the last 24 h and record it in the case report form. All patients will receive brain imaging, including CT, CTA, and CTP examination, at least twice, before the operation and 5–8 days after the operation. Postoperative days 5–8 correspond to the peak period of CVS appearance 7–10 days after aSAH. Imaging aims to assess CTA vasospasm, cerebral perfusion, new hemorrhage (if present), and infarction. CT needs to be examined an additional two times, one within 24 h after the operation to assess whether new cerebral infarction or hemorrhage is caused by surgery and one at discharge to assess the occurrence of new cerebral infarction. The assessments will be completed mainly by an independent radiologist. All TCD monitoring will be performed by an experienced and specialized follower on the day before surgery (T0) and on the immediate (T1), 1st (T2), 2nd (T3), 3rd (T4), 5th (T5), 7th (T6), and 9th (T7) days after the operation. Delirium will be documented using the CAM-ICU during the first 3 days after the operation. Additionally, cognitive performance will be assessed at baseline and at 24 h, 7 days, 30 days, and 90 days after surgery using the Mini-Mental State Examination (MMSE). The modified Rankin scale (mRS) will be used to assess patient disability at discharge and at 90 days. The incidence of complications, including myocardial infarction, postoperative rebleeding, moderate and severe brain edema, pulmonary embolism, deep venous thrombosis, SGB-related complications, and unexpected adverse events, will also be recorded. All baseline and intraoperative data will be recorded by the resident anesthesiologists and the attending anesthesiologists who are responsible for recruitment and intervention.

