### Secondary outcomes

The secondary outcomes in the BLOCK-CVS trial include the following:Incidence of TCD vasospasm within 14 days after aSAH [34].Incidence of CTA vasospasm on days 5–8 after the operation [34].Incidence of abnormal perfusion monitored by CTP on days 5–8 after the operationIncidence of new cerebral infarction observed on days 5–8 after the operation and at dischargeContinuous cerebral blood flow velocity monitored by TCD on the day before surgery (T0) and on the immediate (T1), 1st (T2), 2nd (T3), 3rd (T4), 5th (T5), 7th (T6), and 9th (T7) days after the operationThe Mini-Mental State Examination (MMSE) score was assessed at 24 h, 7 days, 30 days, and 90 days after the operationIncidence of delirium as measured by CAM within 3 days after the operationTotal length of stay in the intensive care unit and hospitalModified Rankin Scale (mRS) score at discharge, 30 days, and 90 daysAll-cause mortality up to 90 daysIncidence of complications up to 90 days

See Supplement Part 3 for detailed definitions of all observed indicators.

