### Sample size calculation

At our institution, we have observed a symptomatic vasospasm rate of approximately 45%. The cure rate of SGB in the treatment of progressive CVS was reported as 39% in another trial [31]. Therefore, we hypothesize a positive effect size of 40% for e-SGB compared with the baseline rate. Finally, using PASS 15, a total of 228 patients were needed to detect the difference (27% in the treatment arm vs. 45% in the control arm) in the primary outcome with 80% power and a two-sided alpha of 0.05, allowing for a 5% loss to follow-up. An interim analysis will be performed when 50% of the required sample size is recruited.

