### Statistical analysis

All efficacy and safety analyses will be analyzed on both a per-protocol and intention-to-treat basis. The intent-to-treat (ITT) population will comprise all subjects randomized to receive e-SGB and with the completed assessment of symptomatic CVS. The per-protocol (PP) population will consist of all subjects in the ITT population not identified as protocol violators (i.e., no obvious Horner’s syndrome after e-SGB, etc.). These protocol violations will be shown in a listing. Subjects with puncture interruption and abandonment due to various reasons are considered to have failed e-SGB and will be excluded from any form of analysis. The decision to exclude a subject from the PP population will be made prior to breaking the blind. The primary outcome will be compared between groups using the Cochran–Mantel–Haenszel test. Postoperative cerebral hemodynamic changes measured at multiple planned time points will be compared using repeated-measures analysis of variance (ANOVA) with the Tukey–Kramer test. In addition, repeated-measures ANOVA will be utilized with a mixed-model approach (including time as a random effect), and the specific comparison of the change in each of those measurements between baseline and any specific time point will be tested using linear contrast. For other outcome data, categorical data will be analyzed by the *χ*^2^ test, and continuous data will be analyzed using Student’s *t* test or the Mann–Whitney *U* test. The rates of spasm, death, complications, and length of stay in the hospital and intensive care unit will be compared using Cox proportional hazards models. All analyses will be adjusted by age, sex, preoperative Hunt-Hess score, preoperative Fisher grade, and site of aneurysm. For the missing data, the last observation and the worst-case imputation scenarios will be used as the main interpolation method. A *p* value less than or equal to 0.05 (two-tailed alpha level) will be considered statistically significant.

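### Table 1 schedules a preoperative CAM-ICU, but the delirium outcome, the measurement text and the covariate list give it no role (minor, one secondary outcome)

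*Protocol article*

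**What the plan says.** All places are in the protocol article.

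- **Abstract, Methods/design** names the outcome without a counting rule: "new cerebral infarction, postoperative delirium, and complications up to 90 days after surgery".
- **Secondary outcomes** words it as the incidence "of delirium as measured by CAM within 3 days after the" operation, with no reference to a preoperative result. The section closes with "See Supplement Part 3 for detailed definitions of all observed indicators".
- **Table 1** marks the CAM-ICU in three columns: Pre, Aft and Day 2–6.
- **Measurements** mentions only the postoperative readings: "Delirium will be documented using the CAM-ICU during the first 3 days after the operation". For the MMSE, the same section does name a baseline assessment.
- **Inclusion criteria** admit "preoperative Hunt-Hess grade 1–3". **Exclusion criteria** do not list preoperative delirium or confusion.
- **Statistical analysis** says of the remaining outcomes that "categorical data will be analyzed by the *χ*^2^ test", and then states: "All analyses will be adjusted by age, sex, preoperative Hunt-Hess score, preoperative Fisher grade, and site of aneurysm". Preoperative CAM-ICU status is not in that list.

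**The concern.** The trial plans to record who is delirious before the block, and the article then gives that information no use. A patient who is CAM-ICU positive before surgery and stays positive on the first postoperative day satisfies the outcome as worded, although a block given later could not have prevented the onset of that delirium.

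Two things follow if such patients are counted. First, each arm carries a similar share of events that the block cannot prevent. This pulls the risk ratio towards 1, shrinks the risk difference and lowers power. Second, chance differences between the arms in preoperative delirium feed into the result as noise that a recorded baseline value could remove.

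A smaller inconsistency sits beside this: Table 1 and the Measurements section do not describe the same CAM-ICU schedule.

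**Working it through.** **1. The plan's own figure.** The article gives no rate, power or sample size for delirium. Its only calculation is for symptomatic vasospasm ("27% in the treatment arm vs. 45% in the control arm", 80% power, two-sided alpha 0.05, 5% loss). With the unpooled two-proportion formula:

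n per arm = (1.960 + 0.842)² × (0.45×0.55 + 0.27×0.73) / 0.18² = 7.849 × 0.4446 / 0.0324 = 107.7, so 108.

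108 / 0.95 = 113.7, so 114 per arm and 228 in total. The stated total reproduces and does not depend on how delirium is counted. I carry forward 108 evaluable patients per arm.

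**2. Model for delirium (assumed inputs).** Let b be the share CAM-ICU positive before surgery and p the new-onset rate among those negative before surgery. Assume p = 30% in controls and 18% with the block (risk ratio 0.60), and that every baseline-positive patient is still positive after surgery.

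- If prevalent cases count: event rate = b + (1 − b)p, with 108 per arm.
- Baseline-negative patients only: event rate = p, with 108(1 − b) per arm.
- Power = Φ[(|p₁ − p₂| − 1.96·SE₀)/SE₁], where SE₀ is the pooled and SE₁ the unpooled standard error.

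| b | Rates if prevalent cases count | Risk ratio | Power, prevalent cases count | Power, baseline-negative only |
|---|---|---|---|---|
| 0% | 30.0% vs 18.0% | 0.60 | 54% | 54% |
| 5% | 33.5% vs 22.1% | 0.66 | 46% | 52% |
| 10% | 37.0% vs 26.2% | 0.71 | 40% | 50% |
| 15% | 40.5% vs 30.3% | 0.75 | 35% | 48% |
| 20% | 44.0% vs 34.4% | 0.78 | 30% | 45% |

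Worked line for b = 10%: 0.10 + 0.90×0.30 = 0.370 and 0.10 + 0.90×0.18 = 0.262. The difference is 0.108 instead of 0.120.

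**3. Sensitivity.**
- If only half of baseline-positive patients stay positive, power with prevalent cases counted is 43%, 39% and 34% at b = 10%, 15% and 20%. The loss is smaller but remains.
- Across control rates of 20–40% and risk ratios of 0.5–0.6, with full persistence, the loss is about 4–9 percentage points at b = 5%, 8–15 at 10% and 13–22 at 20%.

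**4. What stratification recovers.** Under full persistence every patient in the baseline-positive stratum has the event, so that stratum says nothing about the treatment effect. A stratified test in all patients then rests on the baseline-negative stratum and has about the power in the last column, without removing anyone.

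**5. Chance imbalance.** The standard deviation of the between-arm difference in baseline positivity is √(2b(1 − b)/108). At b = 15% this is √(0.255/108) = 0.049, or 4.9 percentage points.

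**The case against.** A reader might infer that the trial counts any positive postoperative CAM as an event whatever the baseline. The document does not say so. Incidence can mean new cases, postoperative delirium can mean delirium that begins after surgery, and the detailed definitions are referred to Supplement Part 3, which is not shown. The preoperative reading in Table 1 may itself be a sign that the investigators mean to separate prevalent from new delirium. This stands: the counting rule is unknown, not wrong. The wording does not settle it the other way either. The same list uses incidence for TCD and CTA vasospasm without a baseline condition, and adds the word new for infarction but not for delirium.

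A reader might also infer bias between the arms. That is not supported. Randomisation balances prevalent delirium in expectation, and the test's error rate already allows for ordinary chance imbalance. Adjustment for Hunt-Hess score may also absorb part of the effect.

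Counting all delirium within three days in all randomised patients is a legitimate outcome, and the secondary comparison is weakly powered on these inputs even with no prevalent delirium (54%). Both points stand. They are reasons to keep the full population and gain precision by adjustment, rather than to insist on one counting rule.

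What the objection does not reach is the article's own text. The covariate list is stated for all analyses and omits the preoperative CAM-ICU, and Measurements does not match Table 1.

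**Conclusion.** The point holds as a minor one. The article schedules a preoperative CAM-ICU and gives it no role in the outcome wording, the measurement text or the stated covariates. As worded, delirium already present before the block can count as an event. The consequence would be dilution and noise, not bias, in one secondary outcome.

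The size cannot be fixed from the document. It rests on assumed new-onset rates, an assumed effect, an assumed baseline prevalence and assumed persistence. On the base-case inputs the loss is about 6 percentage points of power at 5% prevalence, 10 at 10% and 15 at 20%. It is nil if no enrolled patient is delirious before surgery, or if Supplement Part 3 already removes baseline-positive patients. The primary outcome is not touched.

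**What to change.** - **Statistical analysis:** for the delirium outcome, add preoperative CAM-ICU status as a stratum or covariate in all randomised patients. A stratum (Cochran–Mantel–Haenszel, the method already named for the primary outcome) is the safer form, because a logistic model would fail to converge properly on that covariate if every baseline-positive patient stayed positive.
- **Supporting analysis:** report new-onset delirium within 3 days in patients who were CAM-ICU negative before surgery.
- **Secondary outcomes:** state how a positive preoperative CAM-ICU is handled, in agreement with Supplement Part 3.
- **Measurements:** add the preoperative CAM-ICU so that the text matches Table 1.

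The cost is a few lines of wording, settled before unblinding. No new assessment is needed, since Table 1 already schedules it. The supporting analysis uses somewhat fewer patients; the main delirium analysis loses none.

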**Discussion:**

This is a randomized controlled trial to explore the effectiveness and safety of early stellate ganglion block as a preventive treatment to reduce cerebral vasospasm in patients with aneurysmal subarachnoid hemorrhage. If the results are positive, it may provide a new direction for the prevention and treatment of cerebral vasospasm and delayed cerebral ischemia.

**Trial registration:**

The study was registered on Clincaltrials.gov on December 13, 2020 (NCT04691271).

**Supplementary Information:**

The online version contains supplementary material available at 10.1186/s13063-022-06867-9.

## Background

Aneurysmal subarachnoid hemorrhage (aSAH) is a serious life-threatening disease caused by blood flowing into the subarachnoid space after a ruptured intracranial aneurysm. The worldwide incidence of aSAH is approximately 9.1/100,000 people/year [1–3]. In the past 30 years, surgical treatment of ruptured aneurysms has greatly reduced the risk of aneurysm rerupture, and global case mortality has been reduced by 17 to 50% [4–7]. Substantial progress has been made in the treatment of ruptured aneurysms, but little progress has been made in the prevention and treatment of delayed cerebral ischemia (DCI) associated with cerebral vasospasm (CVS). Consequently, DCI after aSAH, especially that associated with CVS, remains a major cause of death and long-term disability, and the disability rate is greater than one-third [4, 5].

CVS is considered a vital underlying mechanism, although the formation mechanism of DCI is not clear. Studies have shown that the incidence of CVS is more than 70%, of which 20–30% of cases can cause DCI [5–8]. Increasing evidence supports that the inflammatory cascade and early brain injury (EBI), which continue and cause various brain pathophysiologies within the first 72 h after bleeding, may be important factors in the formation of CVS and DCI [2, 9–12]. Of these, neuroinflammation is related to almost all pathological processes contributing to CVS or DCI. Thus, it can be understood why all pharmacologic measures based only on vasodilatory properties demonstrate limited efficacy, and even nimodipine is believed to exert its beneficial effect by neuroprotective mechanisms rather than its vasodilatory properties [2, 13]. Blocking inflammation-mediated processes in an early and timely manner may be a more therapeutically effective way to reduce CVS or DCI and improve clinical outcome. Despite years of effort, some tertiary medical centers still report that the incidence of symptomatic or radiographic vasospasm is unacceptably high, at 20–50% or as high as 70% [14–20], respectively. Thus, the prevention and treatment of CVS and DCI is still a major clinical problem.

The stellate ganglion (SG) belongs to the sympathetic ganglion, formed by a fusion of the inferior cervical and first thoracic sympathetic ganglia. It can modulate the immune response, diminish inflammation, and improve cerebral perfusion, as confirmed by numerous studies [21–29]. Current studies have tried stellate ganglion block (SGB) in aSAH patients with diagnosed CVS and observed beneficial outcomes [23, 29–33]. However, early prevention of CVS seems to be more meaningful than treatment of progressed CVS. The modulating effect of SGB on the immune system and its improvement of cerebral perfusion to reduce EBI provide the possibility for the prevention of CVS and DCI. However, the causal relationship between early SGB (e-SGB) and CVS prevention has not yet been established. We designed this study to explore the effectiveness and safety of e-SGB as a means of CVS prevention. We hypothesize that early use of SGB is safe and effective in reducing the incidence of CVS. The results will provide basic evidence for prophylactic e-SGB for CVS and even DCI.

## Methods

### Objective

This trial aims to explore the effectiveness and safety of early stellate ganglion block as a preventive treatment for cerebral vasospasm and delayed cerebral ischemia by observing the incidence of symptomatic vasospasm within 14 days after aSAH.

### Trial design

This trial is a prospective, randomized, open-label, blinded endpoint assessment superiority study that is in line with the Standard Protocol Items: Recommendations for Interventional Trials (SPIRIT 2013). Its two parallel arms do not cross each other, and the random distribution probability is the same. A total of 228 aSAH patients will be randomized within 48 h of symptom onset to an intervention group receiving an additional e-SGB before aneurysm clipping or to a control group undergoing only a routine treatment procedure. The end of follow-up will be 90 days after surgery. The schedule of events for the enrollment, interventions, and assessments of participants is shown in Fig. 1 and Table 1.

**Fig. 1 Fig1:**
[figure not shown]
Study implementation flow chart. The follow-up was completed by a special blinded team, including neurologists, radiologists, nurses, and graduate students. Asterisk symbol (*) indicates that the following time node starts from this moment. Hunt-hess, Hunt and Hess grading; mFisher, modified Fisher grading; GCS, Glasgow Outcome Scale; TCD, transcranial Doppler ultrasound; SGB, stellate ganglion block; HR, heart rate; BP, blood pressure; SpO_2_, pulse oxygen saturation; PaCO_2_, arterial partial pressure of carbon dioxide; EtCO2, end-tidal carbon dioxide; T, temperature; UV, urine volume. BIS, bispectral index; ICU, intensive care unit; AEs, adverse events; CAM-ICU, Confusion Assessment Method for the Intensive Care Unit; MMSE, Mini-Mental State Examination; mRS, modified Rankin Scale

**Table 1 Tab1:** SPIRIT flow diagram

Time point (from onset)	Operation			Post-operation follow-up				
	**Pre**	**Dur**	**Aft**	**Day**	**Day**	**Day**	**Discharge**	**Day 30 or**
	**Day 1–2**			**2–6**	**7–10**	**10–14**		**Day 90**
**Enrollment**								
Eligibility screen	✖							
Recruitment	✖							
Consent	✖							
Randomization and allocation	✖							
**Interventions**								
SGB	✖							
Camouflage action (non-SGB)	✖							
Block-related information	✖							
**Assessments**								
Baseline variables	✖							
Neurological examination	✖		✖	✖	✖	✖	✖	
Physiological parameters	✖	✖	✖	✖	✖	✖	✖	
MMSE	✖		✖		✖		✖	✖
CAM-ICU	✖		✖	✖				
mRS							✖	✖
TCD	✖		✖	✖	✖	✖		
CT	✖		✖		✖		✖	
CTA/CTP	✖				✖			
Complications		✖	✖	✖	✖	✖	✖	✖
All adverse events		✖	✖	✖	✖	✖		
Length of stay							✖	
All-cause mortality							✖	✖

*SGB* Stellate ganglion block, *TCD* Transcranial Doppler, *MMSE* Mini-Mental State Examination, *CAM-ICU* Confusion Assessment Method for the Intensive Care Unit, *mRS* modified Rankin scale, *CT* Computed tomography, *CTA* Computed tomography angiography, *CTP* Computed tomography perfusion imaging

### Location and setting

This trial intends to recruit subjects from Beijing Tiantan Hospital, Capital Medical University, from July 1, 2021, to December 30, 2023.

### Patient population

#### Inclusion criteria

Patients with aSAH diagnosed by imaging (CTA or DSA) and scheduled for surgical intervention within the expected time period (48 h) will be assessed for recruitment. Those with an onset more than 48 h prior to assessment will not be included because CVS can occur on the third day after onset. The inclusion criteria were as follows: (i) 18 years ≤ age ≤ 65 years, (ii) planned aneurysm clipping, (iii) preoperative Hunt-Hess grade 1–3, and (iv) signed informed consent.

#### Exclusion criteria

Patients meeting at least one of the following exclusion criteria will be considered ineligible to participate: (i) ASA physical status > III; (ii) posterior circulation aneurysm, ophthalmic aneurysm, or internal carotid aneurysm; (iii) multiple aneurysms; (iv) coagulation dysfunction; (v) trauma and local infection in the nerve block area; (vi) neck anatomic structural changes (caused by radiotherapy, chemotherapy or surgery); (vii) poor temporal window signal revealed by preoperative transcranial Doppler; (vii) middle cerebral artery stenosis or infarction found by preoperative imaging; (ix) allergy to known local anesthetics; or (x) pregnant or lactating women or those unwilling to sign the informed consent form.

